## 2. Materials and Methods

### 2.1. Study Design and Setting

This project will be a prospective, randomized, double-blind, placebo-controlled clinical trial designed to evaluate the efficacy and safety of NBO therapy in patients diagnosed with CRC undergoing chemotherapy. The study will be conducted in a tertiary hospital setting, ensuring access to standardized treatment protocols and comprehensive patient monitoring. Only NBO operators responsible for therapy administration will be unblinded in order to ensure proper intervention delivery.

### 2.2. Ethical Considerations

This study was approved by the Bioethics Committee at the Lower Silesian Medical Chamber in Wroclaw, Poland (approval no. 06/PN/2025, date: 10 July 2025). The study protocol has been registered at ClinicalTrials.gov (no. NCT06946004, date: 25 April 2025). All patients will be required to give written informed consent before study participation. The study will be conducted in accordance with the guidelines of the Declaration of Helsinki and the principles of Good Clinical Practice (GCP) based on the guidelines of the International Council for Harmonisation of Technical Requirements for Registration of Pharmaceuticals for Human Use (ICH). An up-to-date copy of the study protocol, the current informed consent form for participation in the study, informational documents for study participants, a description of procedures related to participant recruitment, documents related to payments and compensation for study participants resulting from study insurance, and other documents required by the independent Bioethics Committee will be applied. Patients will be informed about voluntary and free participation in the study and about the possibility of withdrawing from the study at any stage without incurring any legal or financial consequences.

### 2.3. Study Participants

The primary study population includes adult patients diagnosed with CRC (ICD10: C18–C20) undergoing chemotherapy. CRC patients commonly experience anemia, immune suppression, and oxidative stress as side effects of chemotherapy, which this study aims to address with NBO therapy. The selected study population is highly relevant due to the significant challenges CRC patients face during chemotherapy, including anemia, oxidative stress, and immune suppression, which impact both treatment outcomes and quality of life. NBO therapy holds potential as a supportive treatment to mitigate these adverse effects.

### 2.4. Eligibility Criteria

Inclusion criteria: (1) age between 18 and 80 years (participants must be adults); (2) diagnosed with CRC (stage II–IV, scheduled for standard chemotherapy (for the study and control groups); (3) baseline hemoglobin levels above 10 g/dL; (4) no concurrent hematologic malignancies; (5) an eastern Cooperative Oncology Group (ECOG) performance status of 0–2 (ensuring that participants are ambulatory and capable of self-care); (6) a life expectancy of at least 12 months (participants are expected to survive for the duration of the study); (7) the ability and a willingness to comply with all study procedures and schedules (including NBO therapy sessions and follow-up visits); (8) adequate organ function as determined by laboratory tests (liver function tests (ALT, AST) and renal function tests (serum creatinine, eGFR)); (9) women of childbearing potential must have had a negative pregnancy test prior to enrollment and agreed to use effective contraception during the study (to ensure safety for potential pregnancies); and (10) written informed consent was obtained prior to any study-related procedures (participants must understand and agree to all aspects of the study).

Exclusion criteria: (1) age under 18 years or over 80 years; (2) severe cardiovascular or respiratory conditions (e.g., unstable angina, recent myocardial infarction, advanced COPD); (3) severe anemia (hemoglobin < 10 g/dL) or any hemolytic disorder that could confound study outcomes; (4) uncontrolled diabetes mellitus (e.g., HbA1c > 8.0% or poor glycemic control requiring frequent hospitalizations); (5) pregnancy or breastfeeding; (6) severe infection or immunocompromised status unrelated to cancer (e.g., advanced HIV infection); (7) current psychiatric or neurological disorders that could interfere with study participation; (8) participation in other investigational therapies within the last 30 days; (9) a lack of written informed consent for study participation; (10) autoimmune or inflammatory conditions (e.g., lupus, rheumatoid arthritis on immunosuppressive therapy) that significantly alter immune responses; and (11) the presence of any contraindication for NBO therapy (e.g., active bleeding, acute infections, inflammation of the optic nerve, epilepsy or seizures, uncontrolled diabetes as noted above, pneumothorax, emphysema, electronic implants).

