Anemia is a common complication in cancer patients undergoing chemotherapy, often due to myelosuppression, where the bone marrow’s ability to produce blood cells is suppressed by cytotoxic agents, and reduced EPO production due to kidney damage [16]. EPO is a glycoprotein hormone primarily produced by the kidneys, which stimulates red blood cell formation (erythropoiesis) in the bone marrow. NBO may enhance erythropoiesis under hypoxia conditions by increasing oxygen availability, thereby improving kidney oxygenation and stimulating EPO synthesis [24]. NBO leads to a reduction in oxidative stress in the kidneys that may cause less chemotherapy-induced damage to the kidney parenchyma and thus ensure the viability of EPO-producing cells [25,26]. Hypoxia plays a key role in both normal and pathological cellular processes, influencing EPO gene expression. Extracellular superoxide dismutase (EC-SOD) has been identified as a critical regulator of this response, acting to suppress hypoxia-induced EPO expression. This suggests that superoxide functions as a signaling molecule in the regulation of EPO production, with its downstream effects partially mediated by hypoxia-inducible factor 1-alpha (HIF-1α) [17].

Over the past decade, concerns have grown about the risks of transfusions associated with cancer treatment. Furthermore, no clear evidence has arisen about the benefits of transfusion and questions about increasing mortality have even been raised. The use of a red blood cell progenitor enhancer such as exogenous EPO is extensively recognized, and a relatively low rate of adverse effects has been reported in patients adequately followed in medical institutions. However, the price of such medications is very high and their availability is limited in some countries. A recently described phenomenon called the ‘normobaric oxygen paradox’ (NOP) may show possible clinical applications [27].

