### 2.5. Randomization and Blinding

Participants will be randomized in a 1:1 ratio to the active NBO (study) or placebo NBO (control) group using a stratified randomization method. Stratification factors include CRC stage (II vs. III vs. IV) and baseline hemoglobin levels (<12 g/dL vs. ≥12 g/dL), as these variables can significantly influence treatment outcomes and the incidence of anemia. A computer-generated allocation sequence will be used within each stratum to ensure an even distribution of these characteristics across the two study arms. Only the NBO operators (who are not involved in data collection or analysis) will have access to the allocation list to administer the assigned intervention. All other study personnel and participants will remain blinded to group assignments.

Patients and clinical staff (excluding NBO operators who administer the therapy) will be blinded to the treatment allocations. Placebo NBO sessions mimic active NBO conditions without therapeutic oxygen adjustments. Both patients and clinical staff involved in patient care and data collection will be blinded to the treatment allocations. NBO operators who administer the therapy will not be blinded in order to ensure the correct delivery of the intervention. They will be trained to maintain confidentiality and avoid any disclosures that could compromise blinding. Both active NBO and placebo NBO sessions will be conducted in chambers that are identical in appearance and setup. This includes similar equipment, procedures, and environmental conditions in order to prevent patients and blinded staff from discerning group assignments.

Unblinding will occur after the database is locked and completion of statistical analysis. Immediate unblinding is permissible in medical emergencies where treatment knowledge is essential for patient care. Unblinding may occur immediately if a serious adverse event or medical emergency arises where knowledge of the treatment allocation is essential for the patient’s safe and effective management. The decision to unblind in an emergency will be made by the principal investigator or a designated medical officer.

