### 2.7. Research Plan

The patient assessment scheme contains six visits from V0 to V5 with subsequent analytical packages with a detailed explanation provided in Section 2.8. The patient assessment schedule consists of six visits, from V0 to V5, each including specific evaluations and interventions. The study will begin with V0 (prequalification/screening), where patient consent will be obtained, medical history will be collected, and baseline data will be recorded. V1 (randomization and pre-test visit) will involve the initial assessments, including anemia, stress, immune function, genetic markers, and patient-reported outcomes (PROMs). Following this, the first phase of the NBO intervention (sessions 1–5) will take place over five weeks. At V2 (midpoint evaluation), the same set of assessments will be repeated to track progress, followed by the second phase of the NBO intervention (sessions 6–10) conducted over the next five weeks. V3 (finalization and post-test visit) will mark the completion of the intervention, with a final round of primary and secondary outcome assessments. The study will then proceed with two follow-up visits: V4 (3 months post-NBO) and V5 (6 months post-NBO), where anemia, stress, immune function, genetic markers, and PROMs will be reassessed to evaluate the long-term effects of the intervention. Table 1 presents the research plan (Figure 1).

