### 2.8. Primary Outcomes

#### 2.8.1. ANEMIA Package

This set captures anemia-related biomarkers and systemic effects, including: (1) EPO and HIF-1α (for assessing erythropoiesis and hypoxia response); (2) 5-diff blood morphology (to provide a detailed blood profile); (3) creatinine + eGFR (kidney function markers for a comprehensive evaluation of metabolic status); (3) ALT + AST (liver function markers for a comprehensive evaluation of metabolic status); (5) glucose and insulin (metabolic and glycemic control); (6) lipid panel (overall lipid profile related to systemic health); (7) iron metabolism (TIBC, Iron, Ferritin) and B12 (to evaluate iron stores and deficiency-related anemia); and (8) albumin and CRP (markers of inflammation and nutritional status). In addition to EPO and HIF-1α, we will measure reticulocyte count as a direct indicator of bone marrow response to assess dynamic changes in erythropoiesis.

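### Iron, TIBC, ferritin and B12 are listed as primary outcomes although their purpose is diagnostic, and the named between-arm test cannot use their baseline values

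*Protocol article*

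**What the plan says.** All references are to the protocol article.

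- **Entry (2.4).** Patients need "baseline hemoglobin levels above 10 g/dL". Exclusion 3 removes "severe anemia (hemoglobin < 10 g/dL) or any hemolytic disorder that could confound study outcomes". Active bleeding is excluded among the contraindications to the intervention. No criterion mentions iron or B12 deficiency.
- **Outcomes (2.8.1, under the heading Primary Outcomes).** Item 7 of the ANEMIA package is "iron metabolism (TIBC, Iron, Ferritin) and B12 (to evaluate iron stores and deficiency-related anemia". The stated purpose is thus to describe iron stores and identify one cause of anemia.
- **Timing (2.7 and Table 1).** The package is measured at the randomization visit: "V1 (randomization and pre-test visit) will involve the initial assessments, including anemia, stress, immune function". It is repeated at V2 to V5.
- **Randomization (2.5).** "Stratification factors include CRC stage (II vs. III vs. IV) and baseline hemoglobin levels (<12 g/dL vs. ≥12 g/dL". Iron and B12 status are not factors.
- **Analysis (2.10).** The arms are compared with the Mann–Whitney U test. Repeated measures are analysed with ANOVA or the Friedman test, and no covariate is named. Sensitivity analyses under other models are promised but not described.
- **Sample size (2.10).** 127 per group, including 30% dropout, two-sided 5% level, 80% power, sized on an erythropoiesis measure for which EPO is the example. No value of d or SD is given.

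**The concern.** There are two linked problems, and both come from what the article states.

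First, the four markers are poor efficacy outcomes. Stimulated red-cell production uses iron, so ferritin can fall when the intervention works. A fall can also mean that the patient is becoming deficient. With no direction of benefit, a difference between arms on these markers cannot be read as success or failure, yet they sit in the primary set.

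Second, the same markers at V1 are natural baseline covariates for hemoglobin and reticulocytes. The Introduction says "Anemia is a common complication in cancer patients undergoing chemotherapy, often due to myelosuppression" and rests the case for the intervention on EPO and red-cell production. A patient short of iron or B12 may turn the same EPO signal into fewer red cells. If so, entry deficiency is a source of variance and possibly an effect modifier on the outcomes that measure production directly. The named test ignores it although the data are collected. At stake is precision on the first objective (reducing anemia) and the reading of a null result.

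**Working it through.** **1. The plan's own figure.** The article gives no d, so 127 cannot be reproduced from its inputs; d has to be back-solved. With n per arm = 2(1.960 + 0.842)²/d², d = 0.42 gives 89. Then 89/0.70 = 127.1, which rounds up to 128 and is close to the stated 127. So 89 evaluable per arm and d = 0.42 are working assumptions. They belong to the sized measure (EPO is the example) and are borrowed here for hemoglobin or reticulocytes only to show scale.

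**2. Possible dilution.** Let f be the share deficient at entry and r their response relative to replete patients, with the SD held constant. Pooled d = 0.42 × [1 − f(1 − r)]. Power = Φ(d√(n/2) − 1.96) plus the negligible opposite tail, with n = 89. Both f and r are assumptions. Replete-only power uses 89(1 − f) per arm at d = 0.42.

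| f | Pooled d, r = 0 | Power, r = 0 | Pooled d, r = 0.5 | Power, r = 0.5 | Replete only |
|---|---|---|---|---|---|
| 0% | 0.420 | 80% | 0.420 | 80% | 80% |
| 30% | 0.294 | 50% | 0.357 | 66% | 65% |
| 40% | 0.252 | 39% | 0.336 | 61% | 58% |
| 50% | 0.210 | 29% | 0.315 | 56% | 51% |

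With r = 1 nothing is lost. With r = 0.5 the pooled analysis is slightly better than the replete subset, so the subset should not replace it.

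**3. Noise.** If deficient patients' hemoglobin change differs by Δ from that of the others, the share of variance explained is R² = f(1 − f)Δ² / [1.2² + f(1 − f)Δ²], with an assumed within-group SD of 1.2 g/dL.
- f = 30%, Δ = 1.0 g/dL: 0.21/(1.44 + 0.21) = 0.127, and 1/(1 − 0.127) = 1.15.
- f = 50%, Δ = 1.5 g/dL: 0.5625/(1.44 + 0.5625) = 0.281, and 1/(1 − 0.281) = 1.39.

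Under these assumptions adjustment is worth 15–39% more patients. Put as power from a starting 80%, R² of 0.10 or 0.20 gives 84% or 88%. Adjustment gains precision; it does not undo dilution.

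**4. Chance imbalance.** At 40% deficient, the 95% range for the difference in prevalence between arms is ±1.96√(2 × 0.4 × 0.6/n): about ±12 percentage points with 127 per arm and ±14 with 89. This is random, not systematic.

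**5. What an interaction term can show.** SE = √(2/[n f(1 − f)]) in SD units, n = 89. With r = 0 the difference in effects is 0.42.
- f = 30%: SE 0.327, z = 1.28, power 25%.
- f = 40%: SE 0.306, z = 1.37, power 28%.
- f = 50%: SE 0.300, z = 1.40, power 29%.

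With r = 0.5 the difference is 0.21 and power is about 10–11%.

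**The case against.** The strongest reply has five parts.

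- **Dilution is conjecture.** It needs both a share of deficient patients and a weaker response in them, and the article gives neither. This stands, and it limits the claim to what may happen.
- **Wrong endpoint for the power figures.** The trial was sized on a measure such as EPO, and a lack of iron or B12 leaves the EPO signal itself intact. This stands. The point covers hemoglobin and reticulocytes only, and the table is illustrative.
- **No bias and no contradiction.** A reader might infer that excluding hemolysis as a confounder obliges the trial to exclude deficiency too, or that deficiency confounds the result. Neither follows. Randomization balances deficiency on average, and a trial may exclude one cause of anemia without excluding all. Stratifying on hemoglobin at 12 g/dL and excluding active bleeding also help somewhat, though neither identifies deficiency.
- **Covariates belong in the analysis plan.** This is fair for what is merely absent; an unseen plan may name covariates. It does not answer the two positive choices in the text: the markers are placed under Primary Outcomes, and the between-arm test named is one that cannot adjust.
- **Iron is not the only misplaced item.** Section 2.8.1 also lists creatinine, liver enzymes, lipids and glucose among primary outcomes. True, but the four markers have the added problem of an ambiguous direction and an obvious better use as baseline variables.

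**Conclusion.** The point holds in a limited form. Iron, TIBC, ferritin and B12 are misplaced as primary outcomes, and the stated between-arm test leaves their V1 values unused. That rests on the text alone.

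The consequence for hemoglobin and reticulocytes is possible noise and possible dilution, of unknown size. The illustrative range runs from no loss (r = 1) through 66–56% power (half response) to 50–29% (no response) at 30–50% deficient. It assumes 89 evaluable per arm and a back-solved d = 0.42 carried over from another endpoint. The no-response case is the extreme.

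Two stronger readings are tempting and not supported. One is that a real effect is diluted as a matter of fact; the article gives no figure from which to conclude that. The other is that adding iron status would let the trial tell a lack of effect from a lack of iron. With interaction power of 25–29% at best, it could not do so reliably. The case for change is better-defined outcomes and a cheap gain in precision.

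**What to change.** - **Section 2.8.1:** move iron, TIBC, ferritin and B12 from the primary outcomes to baseline and explanatory variables. They can still be measured and summarized by arm at every visit.
- **Section 2.10:** compare arms on hemoglobin and reticulocytes with a baseline-adjusted model, for example ANCOVA, on ranks or transformed values if the distribution requires it. Include the V1 value of the outcome, the two stratification factors, and V1 iron and B12 status.
- **Section 2.10:** report the treatment-by-iron-status estimate as supportive and exploratory, and say that its power is low: about 25–29% even if deficient patients do not respond at all, assuming 89 per arm, d = 0.42 and 30–50% deficient.

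No new assay and no change to eligibility or randomization is needed. V1 is also the randomization visit, so stratifying on these results would require them earlier; using them as covariates does not. The cost is a slightly more complex model and one imprecise supportive estimate. Section 3 schedules the first enrollment for March 2026, after the article's publication in July 2025, so on that timetable the change could be specified before any data are seen.

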### 2.5. Randomization and Blinding

Participants will be randomized in a 1:1 ratio to the active NBO (study) or placebo NBO (control) group using a stratified randomization method. Stratification factors include CRC stage (II vs. III vs. IV) and baseline hemoglobin levels (<12 g/dL vs. ≥12 g/dL), as these variables can significantly influence treatment outcomes and the incidence of anemia. A computer-generated allocation sequence will be used within each stratum to ensure an even distribution of these characteristics across the two study arms. Only the NBO operators (who are not involved in data collection or analysis) will have access to the allocation list to administer the assigned intervention. All other study personnel and participants will remain blinded to group assignments.

Patients and clinical staff (excluding NBO operators who administer the therapy) will be blinded to the treatment allocations. Placebo NBO sessions mimic active NBO conditions without therapeutic oxygen adjustments. Both patients and clinical staff involved in patient care and data collection will be blinded to the treatment allocations. NBO operators who administer the therapy will not be blinded in order to ensure the correct delivery of the intervention. They will be trained to maintain confidentiality and avoid any disclosures that could compromise blinding. Both active NBO and placebo NBO sessions will be conducted in chambers that are identical in appearance and setup. This includes similar equipment, procedures, and environmental conditions in order to prevent patients and blinded staff from discerning group assignments.

Unblinding will occur after the database is locked and completion of statistical analysis. Immediate unblinding is permissible in medical emergencies where treatment knowledge is essential for patient care. Unblinding may occur immediately if a serious adverse event or medical emergency arises where knowledge of the treatment allocation is essential for the patient’s safe and effective management. The decision to unblind in an emergency will be made by the principal investigator or a designated medical officer.

### 2.6. Intervention Planned

The intervention will involve NBO as a supportive treatment for CRC patients undergoing chemotherapy. The NBO protocol consists of regular sessions in a normobaric chamber where patients are exposed to controlled oxygen levels aimed at reducing oxidative stress, supporting erythropoiesis, and modulating immune function. Patients in the CRC group will undergo ten NBO sessions across five weeks, with two sessions weekly.

In our study, both the active NBO and placebo NBO groups will undergo sessions in the same normobaric chamber to ensure a consistent experience. For the active NBO group, the chamber will deliver an elevated oxygen concentration (32–40%), while for the placebo group, the oxygen level will be set to approximately 21% (room air). All other environmental parameters—such as chamber pressure, duration of sessions, and ambient conditions—will be identical between the two groups. To maintain the double-blind design, only the NBO operators, who will not be involved in data collection or analysis, will be aware of the specific oxygen settings. Visual indicators of oxygen concentration will be concealed, and the procedure will be standardized so that participants and blinded clinical staff cannot discern which treatment is being administered.

Prior to each NBO session, baseline oxygen saturation (SpO_2_) will be measured using standard pulse oximetry to account for inter-individual variations in oxygenation. If a participant exhibits a significant deviation from their established baseline or displays any clinical signs of respiratory compromise, an arterial blood gas (ABG) analysis will be performed to obtain a more precise measure of oxygenation and guide any necessary adjustments.

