NBO therapy involves delivering oxygen at atmospheric pressure but at a higher fraction than the ~21% found in ambient air. In contrast, hyperbaric oxygen therapy (HBOT) uses both an elevated oxygen concentration and increased atmospheric pressure (typically ≥1.4 ATA), necessitating specialized pressurized chambers [14]. While HBOT has been studied extensively for conditions such as radiation-induced tissue damage, diabetic foot ulcers, and wound healing, NBO offers a more accessible alternative with fewer risks (e.g., lower incidence of barotrauma, reduced logistical constraints) and may be easier to implement in a variety of clinical settings [15]. Mechanistically, NBO may support erythropoiesis, reduce oxidative stress, and modulate immune function through several pathways. First, by delivering a higher oxygen fraction at normobaric pressure, NBO can alleviate tissue hypoxia—including in the kidneys—which may help preserve or enhance endogenous erythropoietin (EPO) production [16]. Second, the improved oxygenation can potentially reduce the generation of reactive oxygen species (ROS) by optimizing mitochondrial function, thereby attenuating oxidative stress and cellular damage [17]. Third, improved oxygen availability in tissues has been hypothesized to counteract tumor hypoxia, which can otherwise promote immunosuppressive mechanisms (e.g., upregulation of immune checkpoint molecules and recruitment of myeloid-derived suppressor cells) [18,19]. Consequently, NBO could restore or enhance immune cell functionality, potentially improving the anti-tumor immune response in cancer patients [20,21,22].

Recent research has explored the potential benefits of NBO in various medical conditions, including its role in supporting erythropoiesis, reducing oxidative stress, modulating immune function, and improving stress, emotional well-being, and cognitive functions in patients [23].

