#### 2.6.1. Active NBO (Study Group)

Patients will be exposed to NBO conditions in Study Group 1 (aNBO), including oxygen levels of 32–40% (compared with about 21% in the atmosphere), pressure maintained at 1500 hPa (compared with about 1000 hPa outside), carbon dioxide levels between 0.7 and 1.9% (compared with 0.03% in the atmosphere), and hydrogen levels between 0.5 and 1% (which is 10,000 to 20,000 times higher than in the atmosphere). The exposure time in the NBO chamber will be the standard 2 h with an additional 20 min for preparation and adaptation and 10 min for finalization and the decompression period.

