#### 2.6.2. Placebo NBO (Control Group)

Patients will be exposed to atmospheric conditions in the same NBO chamber (without normobaric conditions to provide a sham-placebo intervention) in Control Group 2 (pNBO), including oxygen levels at about 21%, pressure maintained at about 1000 hPa, carbon dioxide levels at about 0.03%, and hydrogen levels at about 0.00005% (0.5 parts per million, like in the atmosphere). The primary comparator in this study is the placebo NBO group (n = 127) for CRC patients, which serves to differentiate the specific effects of active NBO from the natural course of treatment without enhanced oxygen exposure.

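### Section 2.6 says the arms differ only in oxygen, but 2.6.1 and 2.6.2 also give them different pressure, CO2 and hydrogen, so the settings test a combined exposure

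*Protocol article*

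**What the plan says.** Section 2.6 (Intervention Planned) sets oxygen at 32–40% in the active arm and about 21% in the placebo arm, and then says: "All other environmental parameters—such as chamber pressure, duration of sessions, and ambient conditions—will be identical between the two groups". Section 2.5 agrees in substance: it describes the sham session as imitating the active one apart from the oxygen adjustment.

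The two subsections that set the chamber conditions say otherwise. Section 2.6.1, for the active arm, has "pressure maintained at 1500 hPa (compared with about 1000 hPa outside), carbon dioxide levels between 0.7 and 1.9" percent, with hydrogen at 0.5–1%, and it allows time for decompression. Section 2.6.2, for the placebo arm, has "pressure maintained at about 1000 hPa, carbon dioxide levels at about 0.03" percent, with hydrogen at about 0.00005%. It calls this arm "without normobaric conditions to provide a sham-placebo intervention" and says that the comparator "serves to differentiate the specific effects of active NBO from the natural course of treatment without enhanced oxygen exposure".

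The Introduction defines the therapy: "NBO therapy involves delivering oxygen at atmospheric pressure but at a higher fraction than the ~21% found in ambient air". It separates this from hyperbaric treatment, which it characterizes by "increased atmospheric pressure (typically ≥1.4 ATA), necessitating specialized pressurized chambers".

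**The concern.** The article defines its arms in two incompatible ways. Staff following 2.6 and staff following 2.6.1 and 2.6.2 would deliver different interventions. Three things depend on which text governs.

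- **The claim.** If only oxygen differs, a positive result is evidence about oxygen. If pressure, CO2 and hydrogen differ as well, it is evidence about the package. The components coincide completely with treatment arm, so no later analysis can separate them. The article leans both ways: 2.6.1 treats the whole package as the NBO condition, while 2.6.2 describes the comparator by its lack of enhanced oxygen, and the Conclusions reason from oxygen availability.
- **The risk wording.** The Introduction's statements about lower barotrauma and pressure risk belong to treatment at atmospheric pressure. As written, they do not describe an arm at 1500 hPa.
- **Blinding.** A chamber pressurized in one arm only may be noticeable to patients. Section 2.6 says that "Visual indicators of oxygen concentration will be concealed", but names no equivalent measure for pressure. Any unblinding would bear mainly on the self-reported PSQ, HADS and EQ-5D, and much less on laboratory outcomes.

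**Working it through.** **Inputs**, all from Sections 2.6.1 (active) and 2.6.2 (sham):

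| Parameter | Active | Sham | Identical, as 2.6 says? |
|---|---|---|---|
| Pressure | 1500 hPa | about 1000 hPa | No, though 2.6 names it |
| CO2 | 0.7–1.9% | about 0.03% | No |
| H2 | 0.5–1% | about 0.00005% | No |
| O2 | 32–40% | about 21% | Intended difference |

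**The plan's own figure.** Section 2.6.1 puts hydrogen at 10,000 to 20,000 times the atmospheric level. This reproduces: 0.5/0.00005 = 10,000 and 1/0.00005 = 20,000. The settings are therefore internally consistent, and a misprint in them is an unlikely explanation.

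**Pressure.** 1500/1000 = 1.5. With 1 ATA = 1013.25 hPa, 1500/1013.25 = 1.48 ATA. The Introduction's hyperbaric mark of 1.4 ATA is 1.4 × 1013.25 = 1418.6 hPa, so the active arm lies above it.

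**Partial pressure = fraction × chamber pressure.**

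- CO2 fraction ratio: 0.7/0.03 = 23 to 1.9/0.03 = 63. Partial pressure: 0.007 × 1500 = 10.5 to 0.019 × 1500 = 28.5 hPa, against 0.0003 × 1000 = 0.3 hPa. Ratio 35 to 95.
- H2 partial pressure: 0.005 × 1500 = 7.5 to 0.01 × 1500 = 15 hPa, against 0.0000005 × 1000 = 0.0005 hPa. Ratio 15,000 to 30,000.
- O2 partial pressure: 0.32 × 1500 = 480 to 0.40 × 1500 = 600 hPa, against 0.21 × 1000 = 210 hPa. Ratio 2.29 to 2.86.

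**The oxygen contrast if 2.6 were right.** At any shared pressure the ratio is 0.32/0.21 = 1.52 to 0.40/0.21 = 1.90.

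**How much of the oxygen contrast is due to pressure.** The ratio factors into a pressure part (1.5) and a fraction part (1.52–1.90), so on the log scale the split does not depend on order:

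- at 32% O2: ln 1.5 / ln 2.286 = 0.49
- at 40% O2: ln 1.5 / ln 2.857 = 0.39

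On the additive scale the share does depend on order. With pressure raised first, air at 1500 hPa gives 315 hPa, so pressure supplies (315 − 210)/(480 − 210) = 39% to (315 − 210)/(600 − 210) = 27%. With pressure raised last, it supplies (480 − 320)/270 = 59% to (600 − 400)/390 = 51%. Across these conventions the share runs from 27% to 59%. It is substantial under any of them.

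**The case against.** The strongest reply is that 2.6.1 and 2.6.2 are the specific operating settings and naturally override a general sentence. The active arm is then a package that 2.6.1 itself calls NBO, the comparator isolates that package, and the randomized contrast is valid. On that view the defect is one wrong sentence and some loose attribution. The validity of the contrast is granted. But the article does not say which text governs, Section 2.5 sides with 2.6, and the sentence names pressure explicitly, so the reader is left to guess.

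Other points on that side:

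- **Size.** The log-scale share is one convention among several, and the large CO2 and hydrogen multiples reflect near-zero sham values. Both are fair. The figures show how far the arms differ; they do not measure bias in any outcome, and the article gives nothing from which that could be calculated.
- **Blinding.** Sections 2.5 and 2.6 also promise chambers that look alike, standardized procedures and operators trained not to disclose. These count in the plan's favour, but none specifically masks a pressure change. Unblinding is possible, not shown.
- **Safety.** The exclusions in 2.4, including pneumothorax and emphysema, and the DSMB in 2.13 are real safeguards. The point here concerns wording and justification.
- **Labels.** The 1.4 ATA mark is qualified as typical, and the sham's description can be read as meaning without the active settings. These are secondary terminology matters.
- **Condensed article.** The full protocol may be consistent. That could reduce the remedy to correcting the article, but two incompatible statements in the published text cannot both be true.

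**Conclusion.** The concern holds. The arms are defined in two incompatible ways, and the difference decides what a positive trial would show. Under the detailed settings the trial estimates the effect of raised oxygen, pressure, CO2 and hydrogen together against room air at ambient pressure. It cannot support a claim about oxygen alone. Pressure is 1.5-fold higher, and the oxygen partial-pressure ratio is 2.3–2.9 instead of the 1.5–1.9 that 2.6 implies.

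This rests on reading the stated settings at face value, treating the sham's approximate values as exact for the arithmetic, and using the standard conversion to ATA. It does not depend on any assumed biological effect of pressure, CO2 or hydrogen. No stated sample-size or power figure changes. The definition of the arms is basic enough that it should be settled before the first patient is enrolled.

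**What to change.** State one set of chamber conditions per arm and use it throughout.

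**If 2.6.1 and 2.6.2 are intended:**
- replace the sentence in 2.6 with one listing the four differences;
- define the tested contrast, and word the conclusions, as the combined exposure against room air at ambient pressure;
- correct the normobaric label, the description of the sham in 2.6.2 and the low-pressure-risk wording, citing the exclusions in 2.4 and the DSMB in 2.13;
- interpret PSQ, HADS and EQ-5D as possibly unblinded, because the sham is not pressurized.

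**If 2.6 is intended:** correct the pressure, CO2 and hydrogen values in 2.6.1 and 2.6.2 so that only oxygen differs.

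Redesigning the sham to match the active arm is optional and has its own trade-offs; full matching would expose sham patients to raised CO2 and hydrogen.

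The cost is an amendment to an ethics-approved, registered protocol, or a correction to the article if the full protocol is already consistent. If 2.6.1 and 2.6.2 stand, the claim is also narrower. No extra patients, visits or measurements are needed, and the sample size in 2.10 stays as it is. First enrolment is planned for March 2026; the article does not show whether it has begun.
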